### Overview of study design

This study is a single-center, open-label, randomly-allocated cohort study, with CKD patients in stages G2, G3a and G3b. To reduce the risk of sampling error, the enrolled patients will be randomly assigned based on the stratified random sampling process by using the random sequence generated by a computer software [22, 23]. The used variables for the stratification will be age (i.e. ≥65, < 65 years old), sex, presence of diabetes mellitus, and eGFR (i.e. ≥46, < 46 ml/min/1.73m^2^). With these four variables, the enrolled patients will be divided into 16 subgroups, and then randomly allocated into the below-described three cohort groups from each of the subgroups.

The enrolled patients will be allocated into the following three cohort groups: 1) sodium bicarbonate group, 2) sodium-potassium citrate group, and 3) standard therapy group without any alkalinizing agents. Then, these three cohort groups will be measured for the targeted biomarkers in the serum and urine in the “short-term” study (i.e. at 0, 6, 12 and 24 weeks after starting the intervention) and in the “long-term” study (i.e. at 1 and 2 years after starting the interventions) to assess the effects of oral alkalinizing agents. As for the urine samples, both early-morning urine and spot urine will be collected. The above-described overview of this cohort study is shown in Fig. 1.

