**Category II (blood test)**	
Ferritin, whole PTH, plasma renin concentration, plasma aldosterone concentration, BNP, erythropoietin, bone specific alkaline phosphatase (BAP), insulin, cortisol, ACTH, leptin, adiponectin, endothelin-1 (ET-1)	

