**Category II (urine test)**	
IgG, transferrin, retino-binding protein (RBP), α1-microglobulin, α2-microglobulin, NAG, Neutrophil Gelatinase-Associated Lipocalin (NGAL), KIM-1, L-FABP, 8-isoprastan, 8-OHdG, type IV collagen, ET-1, angiotensinogen, MCP-1, thioredoxin, IL-1β, IL-6, TNF-α, aldosterone, HCO3^−^, lactate, pH	

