### Endpoints

The primary endpoints will be **1)** the development of significant renal dysfunction, **2)** the occurrence of any kind of cerebrovascular disease between 0 and 24 weeks (short-term study) from starting the interventions. The significant renal dysfunction will be defined as the conditions that fulfill at least one of the following four criteria; 1. serum Cre level ≥ 1.5 times higher than that at 0 week, 2. eGFR decrease ≥20 ml/min/1.73m^2^ from that at 0 week, 3. proteinuria ≥3.5 g/gCr, 4. new development of urinary stones. The secondary endpoints will be the above-described criteria at 1 and 2 years (long-term study) from starting the interventions, and finding any kind of reno-protective marker associated with alkalinizing agents in both periods of study (Table 3).

**Table 3 Tab3:** Primary and Secondary Endpoints

Endpoints	Period	
Primary	Short-term	1) The development of significant renal dysfunction 1. serum Cre level ≥ 1.5 times higher than that at 0 week 2. eGFR decrease ≥20 ml/min/1.73m^2^ from that at 0 week 3. proteinuria ≥3.5 g/gCr 4. new development of urinary stones 2) The occurrence of any kind of CVD and the death
Secondary	Lon-term	1) The development of significant renal dysfunction 2) The occurrence of any kind of CVD and the death
	Short-term & Lon-term	Reno-protective marker associated with alkalinizing agents in both periods of study, for example, category II (blood tests), categoryII (urine test), urine pH and unknown surrogate biomarkers of early renal damage, including uremic toxins and known metabolites measured by metabolomics.

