### Analysis

The measured variables in the three groups will be compared by the analysis of variance (ANOVA), followed by the Bonferroni’s post-hoc comparisons. If the variables show apparent non-normal distributions, Kruskal-Wallis test will be applied as a non-parametric test. Because of the simultaneous multiple comparisons, *p*-value < 0.01 will be regarded as statistically significant. The chronological change of each variable in each group will be also evaluated. Values in each pair will be compared by the paired Student’s t-test. If the variables show apparent non-normal distributions, Wilcoxon’s rank sum test will be adopted. Comparisons of outcome with dichotomous data (i.e. frequency) between the groups will be performed by either of chi-squared test or Fisher’s exact test, based on the achieved frequency in each cell. Lastly, to clarify the correlations between urine pH, both for the early-morning urine and spot urine, and serum creatinine levels, Spearman’s correlation coefficient for each pair will be calculated, followed by the test of no correlation.

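### The fixed p < 0.01 cut-off does not control false positives across the 36 Category II markers, their repeat visits and the metabolomics panel

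*Protocol article*

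**What the plan says.** The Endpoints section of the protocol article lists, as a secondary endpoint, "finding any kind of reno-protective marker associated with alkalinizing agents in both periods of study". Table 3 gives its scope: Category II blood tests, Category II urine tests, urine pH, and "unknown surrogate biomarkers of early renal damage, including uremic toxins and known metabolites measured by metabolomics". The marker search is also the third of the stated objectives.

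The Analysis section compares the three groups variable by variable: they are "compared by the analysis of variance (ANOVA), followed by the Bonferroni’s post-hoc comparisons", or tested by Kruskal-Wallis if clearly non-normal. It then sets the threshold: "Because of the simultaneous multiple comparisons, *p*-value < 0.01 will be regarded as statistically significant". Paired tests of change over time within each group follow. No other multiplicity step is described, and no lead marker is named.

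**The concern.** The protocol gives multiplicity as the reason for its cut-off. A per-test cut-off, however, lets the number of false positives grow in proportion to the number of tests. The Bonferroni step does not help here: as a post-hoc step after ANOVA it adjusts for the three group pairs within one variable, not for the number of variables or visits.

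The marker list is long, is partly measured repeatedly, and is open-ended because of the metabolomics. The only significance criterion that the article offers for a secondary endpoint and an objective would therefore not tell the reader how many of the reported markers to expect by chance.

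**Working it through.** **Inputs**
- Cut-off: 0.01 per test (Analysis).
- Reference error rate: 5%, the only overall type I error rate in the article (Sample size calculation).
- Markers counted from Table 2: 13 Category II blood, 23 Category II urine, 36 in total.
- Visits from Table 1: short-term assessments are "at 0, 6, 12 and 24 weeks after starting the intervention". After baseline, Category II urine is scheduled at all three visits and Category II blood only at 24 weeks. The 1- and 2-year Category II tests depend on earlier abnormal values.
- Metabolomics panel size: not given. I assume 100 to 500 for illustration.

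**1. Where could 0.01 come from?** Three group pairs would give 0.05/3 = 0.0167, and 36 markers 0.05/36 = 0.0014. The value 0.01 equals 0.05/5, but no count of five appears in the article. Under independence, 1 − 0.99^5 = 4.9% and 1 − 0.99^6 = 5.9%, so the cut-off holds 5% for at most five tests.

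**2. Number of tests.** I count one overall three-group test per marker and visit. Short term, after baseline: 13 × 1 + 23 × 3 = 82.

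**3. Error rates if no marker responds.** Expected false positives = 0.01 × m. Under independence, the chance of at least one = 1 − 0.99^m.

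| Tests | m | Expected | At least one |
|---|---|---|---|
| All markers, one visit | 36 | 0.36 | 30.4% |
| Short term, all visits | 82 | 0.82 | 56.1% |
| Same, without urine pH and HCO3− (13 + 21 × 3) | 76 | 0.76 | 53% |
| With 1 and 2 years (13 × 3 + 23 × 5), upper bound | 154 | 1.54 | 78.7% |

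The third row is there because the dose is adjusted to urine pH (Drug intervention). Urine pH, and with it urinary bicarbonate, is meant to change and is not a plausible null.

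**4. Correlation.** A simulation of 20,000 runs with equally correlated normal test statistics gave these chances of at least one false positive at two-sided 0.01:

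| Correlation | 36 tests | 82 tests |
|---|---|---|
| 0.3 | 23.7% | 40.4% |
| 0.5 | 17.0% | 26.7% |
| 0.8 | 7.5% | 10.6% |

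Every figure exceeds 5%.

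**5. Metabolomics.** Per visit, 100 null metabolites give 100 × 0.01 = 1 expected false positive, and 500 give 5.

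**6. False discoveries.** With share π of markers truly responding and power w, the false share of significant results is about 0.01(1 − π) / [0.01(1 − π) + πw]. All values of π and w are assumptions:
- π = 20%, w = 80%: 0.008/0.168 = 5%.
- π = 5%, w = 50%: 0.0095/0.0345 = 28%.
- π = 2%, w = 30%: 0.0098/0.0158 = 62%.

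The fixed cut-off therefore fixes neither the family-wise error nor the false discovery rate.

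**The case against.** **The threshold may never have been meant for markers.** The sentence beginning "Because of the simultaneous multiple comparisons" comes straight after the three-group tests and may refer only to the group comparisons. An adjustment across markers could then sit in an analysis plan that is not shown. This is partly right: the article does not say that 0.01 controls error across markers, and the mere absence of a cross-marker method would be no finding. But the article does fix the threshold for its measured variables. If the phrase covers markers, the rule is too weak; if it covers only group pairs, the stated rule contains nothing for markers.

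**The search is exploratory.** The objective speaks of seeking new markers, and none is put forward for confirmation. That limits the seriousness of the point. It does not repair the rule, because the endpoint is listed as secondary without an exploratory label.

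**The size is easily overstated.** A reader might infer that a false marker is more likely than not even if alkali does nothing. The documents do not support this for the listed markers. The 56% needs 82 independent tests, but 69 of them are 23 urine markers measured three times in the same patients, and a correlation of 0.3 already brings the figure below one half.

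A reader might also add the within-arm paired tests: 82 × 3 = 246 more, 328 in all, 3.28 expected false positives. That sum mixes questions. A within-arm change reflects time as well as treatment, so a real time trend is not a type I error, and no section says that such tests would name a marker.

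Finally, one might read the plan as naming every variable below 0.01 a reno-protective marker. The Analysis section defines only statistical significance.

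**Conclusion.** The point holds in a limited form. The fixed cut-off of 0.01 controls neither the family-wise error nor the false discovery rate over the marker endpoint, whichever way its stated reason is read.

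For the listed markers, the chance of at least one false positive is 30% at a single visit and 56% over the short-term visits under independence (53% without urine pH and HCO3−). It is about 40% to 11% over those visits at correlations of 0.3 to 0.8. These figures assume that no marker responds and that each marker is tested once per visit between arms. The metabolomics contribution rests on an assumed panel size and shows sensitivity only.

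The primary endpoint is unaffected. The change is worth making because a named secondary endpoint depends on the rule.

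**What to change.** For marker claims, replace the fixed 0.01 by Benjamini-Hochberg control of the false discovery rate at q = 0.05:
- Use between-arm comparisons at week 24, the short-term post-baseline visit at which both Category II sets are scheduled.
- Declare three families: Category II blood (13), Category II urine without pH and HCO3− (21), and metabolomics.
- Report weeks 6 and 12 and the within-arm paired tests as supportive only.
- State which comparisons p < 0.01 still governs.

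The cost is analysis wording and a routine adjustment of p-values, with no new patients, visits or assays. Choosing week 24 is a design decision and gives up formal claims from the earlier visits.

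Weak isolated signals may no longer count as significant: a lone blood marker would need p ≤ 0.05/13 = 0.0038. Fewer significant markers are not guaranteed, however. The Benjamini-Hochberg limit for the k-th smallest p-value is 0.05k/m, which exceeds 0.01 once k/m is above 20%; for blood, k = 3 gives 0.0115. Three separate families also leave up to 1 − 0.95^3 = 14% chance of some false claim if nothing responds and the families are independent.

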### Sample size calculation

A sample size was decided based on a previous study evaluating the reno-protective effect of the sodium bicarbonate [20], in which the incidence of ESKD under treatment with and without bicarbonate were 6.5 and 33%, respectively. Based on this knowledge, we presumed the estimated incidence rate of ESKD in the sodium bicarbonate group and the sodium-potassium citrate group to be around 5 and 30%, respectively. To achieve the significant level (i.e. type-I error rate) of 5% (α = 0.05) and the statistical power of 80% (β = 0.2) with the equally allocated three groups, we estimated the ideal sample size in each group to be 50.

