## Objectives

Our objectives are as follows:
To confirm the protective effects of oral alkalinizing agents on renal function in patients with mild and moderate-stages of CKD.To compare the reno-protective effects of two types of oral alkalinizing agents, sodium/potassium citrate and sodium bicarbonate in CKD patients. Their effects will also be compared with that in the standard therapy group without oral alkalinizing agents.To seek for the new surrogate markers in the serum and urine associated with early renal damage that can be cancelled by oral alkalinizing agents.

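### The 80% power rests on ESKD rates that are not the 24-week primary endpoint, and on an untreated risk given to the citrate arm, so it is unsupported for the primary endpoint

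*Protocol article*

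**What the plan says.** The Sample size calculation section starts from an earlier bicarbonate study in which "the incidence of ESKD under treatment with and without bicarbonate were 6.5 and 33%, respectively". It then presumes the "incidence rate of ESKD in the sodium bicarbonate group and the sodium-potassium citrate group to be around 5 and 30" percent, in that order. It sets "the significant level (i.e. type-I error rate) of 5% (α = 0.05") and "the statistical power of 80% (β = 0.2"), and concludes: "with the equally allocated three groups, we estimated the ideal sample size in each group to be 50". No rate is given for standard therapy.

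The Endpoints section and Table 3 define the primary endpoint over weeks 0 to 24. It has two parts:
- significant renal dysfunction, meaning any of "serum Cre level ≥ 1.5 times higher than that at 0 week", an eGFR fall of at least 20 ml/min/1.73m², proteinuria of at least 3.5 g/gCr, or new urinary stones;
- cerebrovascular disease in the text, or CVD and death in Table 3.

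ESKD is not listed there, nor among the secondary endpoints.

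The first objective is "To confirm the protective effects of oral alkalinizing agents on renal function in patients with mild and moderate-stages of CKD". The second compares citrate with bicarbonate, and both with standard therapy. The Discussion hypothesises that alkalinizing agents delay ESKD.

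**The concern.** Two inputs to the sample size do not match the rest of the article.

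1. **Outcome and time window.** The planning rates are ESKD incidences. The primary endpoint is a composite of laboratory thresholds, stones and vascular events over 24 weeks in stages G2 to G3b. The article neither says over what period the ESKD rates accrued nor converts them into a 24-week composite rate.
2. **Arm.** The source contrast is treated against untreated. The plan gives the untreated risk, rounded from 33% to 30%, to citrate. Citrate then has no assumed benefit, which contradicts the second objective and the hypothesis, and the standard arm has no assumed risk.

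At stake is how a non-significant primary result is read. The Discussion allows for a negative result caused by too small a sample and mentions extending the study. That judgement needs a valid statement of what the trial could detect on its primary endpoint. The 80% does not provide one, and a reader who trusts it could take a null result as evidence of no effect.

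**Working it through.** **Inputs from the article.** Planning rates 5% and 30%; alpha 0.05 (sidedness and any split not stated); power 80%; 50 per group; chi-squared or Fisher's exact test for dichotomous outcomes, chosen by cell frequency (Analysis). The Analysis section also declares p < 0.01 because of multiple comparisons, and does not make clear whether that covers the dichotomous primary endpoint.

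**Step 1. Reproduce 50 per group.** Normal approximation with pooled variance:

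n = [z(1−α/2)·√(2p̄(1−p̄)) + z(1−β)·√(p1(1−p1) + p2(1−p2))]² / (p1−p2)²

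Here p̄ = (0.05 + 0.30)/2 = 0.175, √(2×0.175×0.825) = 0.5374, √(0.0475 + 0.21) = 0.5074 and (p1−p2)² = 0.0625.

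- Two-sided 0.05: (1.960×0.5374 + 0.8416×0.5074)² / 0.0625 = 35.06, so 36 per group. With continuity correction it is 43, and Fisher's exact test needs 39.
- Two-sided 0.05/3, for three pairwise comparisons: (2.394×0.5374 + 0.8416×0.5074)² / 0.0625 = 46.98, so 47. With continuity correction it is 55. Fisher's exact test has power 0.788 at 49 and 0.8002 at 50.

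So 50 can be obtained from 5% vs 30%, using Fisher's test and an unstated three-way split of alpha. The arithmetic is not the problem.

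**Step 2. Compare the inputs with the endpoint and the arms.**

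| Item | Sample size calculation | Elsewhere in the article |
|---|---|---|
| Outcome | ESKD | Composite without ESKD (Endpoints, Table 3) |
| Period | Not stated | 0 to 24 weeks |
| Citrate | 30%, close to the source's untreated 33% | Active agent (Objectives) |
| Standard therapy | No rate | Comparator for both agents (Objectives) |

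Read literally, the only contrast with a planned difference is bicarbonate against citrate. If standard therapy also carried 30%, citrate against standard therapy would be 30% vs 30%. There would be no effect to detect, and Fisher's test at 0.05 would reject in about 3% of trials.

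**Step 3. Power for the composite under assumed rates.** The article gives no 24-week composite rate, so the rates below are assumptions. Power is the sum, over all pairs (x, y) for which the test rejects, of Bin(x; 50, p1)·Bin(y; 50, p2). Both tests are two-sided, and chi-squared is without continuity correction.

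| Treated vs standard (assumed) | α = 0.05, chi-squared / Fisher | α = 0.01, chi-squared / Fisher |
|---|---|---|
| 5% vs 30% | 95% / 90% | 82% / 75% |
| 5% vs 20% | 66% / 51% | 38% / 28% |
| 5% vs 15% | 39% / 24% | 16% / 10% |
| 5% vs 10% | 14% / 6% | 3% / 2% |

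The table covers 50 per arm. The article does not give the number actually randomised.

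**The case against.** **The citrate label may be a drafting slip.** The 5% and 30% follow directly from the with and without figures, so citrate may simply stand where standard therapy was meant. This is plausible and would remove the second fault. It would not touch the first: the rates would still be ESKD rates, with no link to the 24-week composite.

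**A reader might infer that the trial is underpowered.** The documents do not support this. The composite rate is unknown in either direction. Its criteria are milder than ESKD, and the proteinuria criterion is an absolute threshold not tied to baseline, with no exclusion for proteinuria at entry. If the composite ran at the plan's own 5% and 30%, 50 per arm would give 95%/90% at two-sided 5%.

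**A reader might infer that bicarbonate against citrate is not a planned comparison.** It is planned. The second objective lists it first, and the article names no primary pairwise contrast. The narrower point stands: the difference assumed for it conflicts with the view that both agents protect.

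**Pooling the two alkali arms might look like a remedy.** At an assumed 5% vs 20%, 100 vs 50 gives 81% by chi-squared but 76% by Fisher. The article does not plan pooling. Recruitment to this open-label trial closed in March 2018 and the article appeared in April 2020, so a new lead contrast could be a choice made with knowledge of the data.

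**The authors concede that numbers may be low.** The Discussion does say so, which softens the risk of misreading. It does not say what the trial can detect on its primary endpoint.

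**Conclusion.** The concern holds in this form: the stated 80% power is unsupported for the 24-week primary endpoint. The outcome used for sizing is not part of that endpoint, and the assumed arm risks contradict the article's own objective and hypothesis. Both facts can be read directly from the text and need no assumption.

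The size of the consequence does depend on assumptions. With a treated rate of 5%, 50 per arm and two-sided 5%, power runs from 95%/90% (chi-squared/Fisher) at a standard-arm rate of 30% down to about 14%/6% at 10%. It is lower throughout if p < 0.01 also governs this endpoint. The finding is neither that 50 per group is miscalculated nor that power is known to be low.

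**What to change.** Rewrite the Sample size calculation section, or issue a correction to it:

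1. Reconcile the 30% between citrate and standard therapy, and state an assumed rate for all three arms.
2. Replace the 80% claim with the power or detectable difference for the 24-week composite, each alkali arm against standard therapy, at the number actually randomised.
3. Give a range of standard-arm composite rates, labelled as assumptions, and use the test and alpha that will be applied. This includes saying whether p < 0.01 covers the primary endpoint.
4. State that bicarbonate against citrate has no supported power once both are assumed protective, and that a null result is not evidence of no effect.
5. Do not introduce a pooled alkali arm as a new lead contrast at this stage.

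The cost is text only. Recruitment is closed, and no patients, visits or arms change. The downside is that the stated power will probably look less favourable than 80%.

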### Analysis

The measured variables in the three groups will be compared by the analysis of variance (ANOVA), followed by the Bonferroni’s post-hoc comparisons. If the variables show apparent non-normal distributions, Kruskal-Wallis test will be applied as a non-parametric test. Because of the simultaneous multiple comparisons, *p*-value < 0.01 will be regarded as statistically significant. The chronological change of each variable in each group will be also evaluated. Values in each pair will be compared by the paired Student’s t-test. If the variables show apparent non-normal distributions, Wilcoxon’s rank sum test will be adopted. Comparisons of outcome with dichotomous data (i.e. frequency) between the groups will be performed by either of chi-squared test or Fisher’s exact test, based on the achieved frequency in each cell. Lastly, to clarify the correlations between urine pH, both for the early-morning urine and spot urine, and serum creatinine levels, Spearman’s correlation coefficient for each pair will be calculated, followed by the test of no correlation.

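### The between-arm marker tests adjust for neither the week-0 value nor the stratification factors, which costs precision, and the only stated tests of marker change are within arms

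*Protocol article*

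**What the plan says.** Analysis section, between arms: "The measured variables in the three groups will be compared by the analysis of variance (ANOVA"), followed by Bonferroni comparisons. For non-normal variables, "Kruskal-Wallis test will be applied as a non-parametric test". The significance threshold is stated as "value < 0.01 will be regarded as statistically significant". No covariate, stratum, repeated-measures model or arm-by-time term is named.

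Analysis section, within arms: "The chronological change of each variable in each group will be also evaluated". The method is "Values in each pair will be compared by the paired" t-test, and for non-normal variables a "rank sum test will be adopted".

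Overview of study design: "The used variables for the stratification will be age", together with sex, diabetes and eGFR, which gives 16 subgroups. Short-term markers are taken "at 0, 6, 12 and 24 weeks after starting the intervention", and long-term markers at 1 and 2 years. Table 1 refines this. Category I tests are done at every visit. Category II urine tests are done at all four short-term visits, but category II blood tests only at weeks 0 and 24. At 1 and 2 years, both sets of category II tests are repeated only where short-term values were abnormal and follow-up seems desirable.

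Objectives: the two agents are to be compared with each other and with standard therapy. Table 3 lists the markers as secondary endpoints in both periods.

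**The concern.** The objectives are comparative, and the trial collects what an efficient comparison needs: a week-0 value for the markers and four factors already judged important enough to stratify on. The between-arm marker tests, as named, use neither. The stated tests that look at change in a continuous marker are run inside one arm at a time. A significant change in one arm and a non-significant change in another does not show that the arms differ.

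At stake is precision on the secondary marker endpoints, tested at a strict threshold in about 50 patients per arm. The Discussion section itself concedes that enrolment may remain low. There is also a risk that a pattern of within-arm p-values is later read as a treatment effect.

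**Working it through.** **The plan's own figures.** The article gives no precision or detectable difference for the markers, so there is none to reproduce. The 50 per group comes from a binary calculation (5% against 30%, alpha 0.05, power 80%). The usual two-sided formula gives 36 per group (43 with continuity correction), so 50 needs further unstated choices. Nothing below depends on that; 50 per arm is taken as given.

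**Inputs.** From the article: n = 50 per arm, threshold 0.01, power 80%. Assumed: two-sided testing, SD = 1 at both times and in all arms, and r from 0.3 to 0.9.

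**Formulas.** Variance of a single value, relative to the follow-up SD:
- ANOVA on follow-up values: 1
- ANOVA on change from week 0: 2(1 − r)
- ANCOVA on week 0: 1 − r²

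ANCOVA relative to follow-up ANOVA is therefore 1 − r². Relative to change ANOVA it is (1 − r²)/[2(1 − r)] = (1 + r)/2.

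Detectable difference for unadjusted follow-up values: √(2/50) × (2.576 + 0.842) = 0.2 × 3.418 = 0.68 SD. Multiply by √(1 − r²) for ANCOVA and by √[2(1 − r)] for change.

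| r (assumed) | ANCOVA / follow-up ANOVA | ANCOVA / change ANOVA | Detectable, follow-up (SD) | Detectable, change (SD) | Detectable, ANCOVA (SD) |
|---|---|---|---|---|---|
| 0.3 | 0.91 | 0.65 | 0.68 | 0.81 | 0.65 |
| 0.5 | 0.75 | 0.75 | 0.68 | 0.68 | 0.59 |
| 0.7 | 0.51 | 0.85 | 0.68 | 0.53 | 0.49 |
| 0.8 | 0.36 | 0.90 | 0.68 | 0.43 | 0.41 |
| 0.9 | 0.19 | 0.95 | 0.68 | 0.31 | 0.30 |

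Power for a true difference of 0.5 SD at alpha 0.01 is 47% with follow-up ANOVA. With ANCOVA it is 52%, 62%, 82%, 94% and over 99% at the five values of r. If Bonferroni for three pairs is applied on top of 0.01 (alpha 0.0033), the detectable differences are 0.76 SD unadjusted against 0.72 to 0.33 SD with ANCOVA; the variance ratios do not change.

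**Within-arm tests.** Suppose all three arms have the same true change and each paired test has power p. The arms disagree on significance with probability 1 − p³ − (1 − p)³. At p = 0.5 this is 1 − 0.125 − 0.125 = 75%. At p = 0.2 or 0.8 it is 1 − 0.008 − 0.512 = 48%. No arm difference exists in either case.

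**Stratification factors.** Their separate gain cannot be computed from the article and is probably smaller once week 0 is in the model. With 150/16 ≈ 9 patients per cell, or about 3 per arm, they should enter as main effects and not as 16 strata.

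**The case against.** The Analysis section does not say at which visits, or on which scale, the ANOVA is run. A reader might infer raw values compared at each visit and, at r = 0.8, a loss equal to 1/0.36 = 2.8 times the patients. The text does not support that as fact. If the ANOVA is run on change, which the wording allows, the same r gives 1/0.90 = 1.1 times. This stands, and it is why both scales are shown. On either scale ANCOVA is at least as precise.

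A reader might also infer that no analysis uses week 0. That is wrong. The creatinine and eGFR criteria of the primary endpoint are defined against week 0 and compared between arms by chi-squared or Fisher's test, and the paired tests presumably use it too. The gap is confined to between-arm tests of the continuous markers.

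The within-arm tests are announced as an addition ("The chronological change of each variable in each group will be also evaluated"), and nowhere does the article plan to infer an arm difference from them. The 75% and 48% figures therefore measure the risk of a misreading, not a planned error.

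Ignoring the strata does not bias the comparison; it tends to make the test conservative. Finally, a condensed article may leave model terms to a fuller document. That has some force, but this article does name the tests, and those tests carry no covariate. The point is about a stated choice that can be improved, not about missing detail.

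**Conclusion.** The point holds as one of efficiency and interpretation. The between-arm marker comparison is valid under randomisation, provided that the randomised patients are measured and kept in the analysis, but it is less precise than the available data allow. For assumed r between 0.3 and 0.9, the adjusted analysis has 9% to 81% less variance than ANOVA on follow-up values, or 35% to 5% less than ANOVA on change. The size rests on r and on the scale, neither of which the article gives. The direction does not depend on them, except that with r = 0 adjustment brings no gain over follow-up values. The within-arm tests do not serve the comparative objectives. The documents do not support a claim of bias or of an inflated false-positive rate in the ANOVA. The endpoints affected are secondary, so this should be changed but does not undermine the primary comparison.

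**What to change.** - Make the between-arm analysis of each continuous marker an ANCOVA at 24 weeks with arm, the week-0 value and the four stratification factors as main effects. Log-transform skewed markers instead of switching to Kruskal-Wallis, which takes no covariate.
- Use a repeated-measures mixed model with an arm-by-visit term only where there are several follow-up visits: category I markers, and category II urine markers in the short term. Category II blood markers have one short-term follow-up (week 24), so ANCOVA is the model there.
- Report arm differences with confidence intervals.
- Label within-arm tests as descriptive. If they stay, the non-normal fallback for paired values should be the signed-rank test; the rank sum test is for independent samples.
- Treat category II comparisons at 1 and 2 years as exploratory, because those patients are selected after randomisation by abnormal short-term results.

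The cost is some analysis and programming time and no new data. As the trial is open-label, the change should be fixed and dated before results by arm are examined.

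### The non-normal fallback for the paired within-group comparisons is the rank sum test, an independent-samples test; with positive within-patient correlation its p-values are too conservative

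*Protocol article*

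**What the plan says.** In the protocol article, Methods, Analysis, the three groups are compared by ANOVA. For non-normal variables, "Kruskal-Wallis test will be applied as a non-parametric test". The section then sets a threshold of p<0.01 and turns to change over time: "The chronological change of each variable in each group will be also evaluated". The parametric test for that is stated next: "Values in each pair will be compared by the paired" t-test. The fallback follows directly: "If the variables show apparent non-normal distributions", Wilcoxon's "rank sum test will be adopted".

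The repeated values come from the short-term visits, "at 0, 6, 12 and 24 weeks after starting the intervention", and from the visits at 1 and 2 years (Overview of study design). The signed-rank test does not appear in the article.

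**The concern.** The two values in each pair belong to the same patient. The paired t-test respects this by working on the within-patient difference. The rank sum test pools the two visits and ranks all values as if they came from two unrelated groups. It therefore uses the variance for independent samples, which is too large when a patient's values at two visits go together. P-values come out too large and real changes are harder to detect.

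The rule covers every variable followed over time. These include the category II blood and urine markers, which Table 3 lists under the secondary endpoints. Concentration markers such as NGAL, KIM-1, IL-6 or BNP may well be skewed. That is an assumption, since the article gives no distributions, but if it holds the fallback would come into use for many of them.

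**Working it through.** **1. Which comparison the sentence governs.** The Analysis section names two non-parametric fallbacks, each opened with the same non-normality condition. Kruskal-Wallis follows ANOVA, so it belongs to the three-group comparison. The rank sum test follows the paired t-test, so it belongs to the within-group pairs. No other reading fits the order of the sentences.

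**2. Inputs.**
- Pairs per group: 50, from the Sample size calculation section ("the statistical power of 80% (β = 0.2) with the equally allocated three groups"). That calculation concerns event rates; it supplies only the number of pairs here. The article gives no power figure for the paired tests, so there is none to reproduce.
- Correlation between a patient's two values on the log scale, ρ: not given. Assumed range 0.3 to 0.8.
- Distribution: log-normal (assumed, to represent a skewed marker).
- Threshold: two-sided 5%. The article also states that p<0.01 "will be regarded as statistically significant", but that sentence stands before the paired tests and does not clearly cover them.

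**3. Type I error by formula.** With no change, the rank sum statistic has true variance (1 − ρ_S) times the variance the test assumes, where ρ_S is the rank correlation. For log-normal pairs ρ_S = (6/π)·arcsin(ρ/2). The real type I error is then 2·[1 − Φ(1.96/√(1 − ρ_S))].

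| ρ (assumed) | ρ_S | 1.96/√(1 − ρ_S) | Real type I error at nominal 5% |
|---|---|---|---|
| 0 | 0 | 1.96 | 5.0% |
| 0.3 | 0.288 | 2.32 | 2.0% |
| 0.5 | 0.483 | 2.72 | 0.6% |
| 0.7 | 0.683 | 3.48 | 0.05% |
| 0.8 | 0.786 | 4.24 | about 0.002% |

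Simulation of 50 pairs agrees: about 2.2% at 0.3, 0.6% at 0.5 and about 0 from 0.7. In a run of 4,000 datasets per setting, the signed-rank test on the raw pairs stayed between 4.4% and 5.4% at every correlation.

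**4. Power for a fixed shift.** Simulation, 50 log-normal pairs, shift of 0.3 SD on the log scale, p<0.05, signed-rank test on raw differences. Relative loss is (signed-rank − rank sum)/signed-rank.

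| ρ (assumed) | Rank sum | Signed-rank | Relative loss |
|---|---|---|---|
| 0.3 | 30% | 37% | 7/37 = 19% |
| 0.5 | 25% | 47% | 22/47 = 47% |
| 0.7 | 21% | 68% | 47/68 = 69% |
| 0.8 | 16% | 82% | 66/82 = 80% |

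Repeat runs agree within about two percentage points.

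**5. Does the result depend on the chosen shift?** A second set of runs sized the shift at each ρ so that a paired test on the log scale has about 80% power at 5%.

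| ρ (assumed) | p<0.05: rank sum vs signed-rank | p<0.01: rank sum vs signed-rank |
|---|---|---|
| 0.3 | 0.68 vs 0.74 | 0.37 vs 0.47 |
| 0.5 | 0.51 vs 0.72 | 0.20 vs 0.47 |
| 0.7 | 0.22 vs 0.71 | 0.04 vs 0.44 |
| 0.8 | 0.08 vs 0.71 | 0.01 vs 0.45 |

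At p<0.05 the relative loss is 0.06/0.74 = 8% at ρ = 0.3, 0.21/0.72 = 29% at 0.5 and 0.49/0.71 = 69% at 0.7. The direction is the same in both settings; the size depends on the correlation and on the shift.

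**The case against.** The wrong test name itself is hard to defend, but its reach can be contested.

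- **It may be a slip.** The sentence follows a paired t-test, so a paired test was probably meant. The article cannot settle this. An analyst who follows the text literally would still run the wrong test, so the correction is needed either way.
- **The error is conservative.** With positive correlation it produces missed changes and not false claims. This stands, and it limits the harm.
- **The analysis is supplementary.** The biomarker endpoint asks which markers are associated with the alkalinizing agents. In a randomized three-group study the between-group comparison mainly answers that, and ANOVA or Kruskal-Wallis is correctly named for it. A change within one group does not separate drug effect from time. This also stands.
- **The primary endpoint is untouched.** It is an event, compared by the chi-squared or Fisher's exact test.

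A reader might infer that most of the power is lost for every skewed marker. The article does not support that. It gives no within-patient correlation, and at 0.3 the relative loss is between 8% and 19% in the two settings examined. More than half is lost at p<0.05 only when correlation is above about 0.5. A reader might also credit the change of test with the power of a signed-rank test on log differences. Part of that gain comes from the transformation: in the second setting, power at p<0.05 is 0.78 to 0.80 on the log scale against 0.69 to 0.74 on raw pairs.

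**Conclusion.** The rule is wrong as written: an independent-samples test is assigned to paired values. The miscalibration follows for any non-zero within-patient correlation, and for positive correlation it is on the conservative side. Its type I error does not depend on the number of pairs. The cost in power runs from small at low correlation to severe when values track strongly within patients. This range rests on an assumed correlation, an assumed log-normal shape and 50 complete pairs per group. How many variables would reach the fallback is unknown from the article. The point is confined to within-group changes of non-normal variables and is graded should-fix.

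**What to change.** In the Analysis section, replace Wilcoxon's rank sum test with the Wilcoxon signed-rank test, applied to within-patient differences between visits. In the same edit, the sponsor could say whether the p<0.01 threshold covers these paired tests. A log transformation of skewed markers is optional and not part of this correction.

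The cost is a change of test name in one sentence. It requires no new data, visits or patients, and leaves the primary and between-group analyses as they are.
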